## **Background**

Video-assisted thoracoscopic surgery (VATS) has become the primary surgical approach in thoracic surgery. Compared with thoracotomy, VATS is notable for less trauma, lower postoperative pain levels, better quality of life, shorter length of hospitalization, and lower complication rates. Despite numerous analgesic strategies in clinical practice, including thoracic epidural analgesia, paravertebral block, and patient-controlled analgesia, acute postoperative pain still exists after VATS.

Acute postoperative pain is closely related to operation time, chest tube duration, and postoperative activities. After surgery, doctors will encourage patients to cough to promote the expulsion of respiratory secretions, but patients may be afraid to cough forcefully due to postoperative acute pain. About 59% of patients experienced moderate to severe acute pain during the first three days after VATS. In contrast, postoperative pain when coughing is often more severe than when resting. Approximately 51.7% of patients experienced moderate to severe pain when coughing within the first 24 hours after surgery. On postoperative day 7, around 20% of patients were still encountering moderate and severe pain while coughing.

Notably, inadequate management of acute postoperative pain frequently results in chronic post-surgical pain (CPSP). About 43.99% of patients reported CPSP after VATS, and the incidence of moderate or severe chronic

pain is 14.71% among them. CPSP will reduce the quality of life of patients and affect their physical and mental health. The efficacy of drug treatment is limited for CPSP at present. Acute postoperative pain control and prevention of CPSP still lack effective interventions.

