## Inclusion criteria:

1. Men or women aged 18 to 75 years
2. Patients diagnosed with NSCLC before or during surgery
3. Undergoing VATS for pulmonary resection (including lung wedge resection, segmentectomy, and pulmonary lobectomy) for the first time
4. American Society of Anesthesiologists physical status I or II 筛选表加
5. Having no communication barriers and can cooperate with 3 months telephone follow-up

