## **Sample size calculation**

Based on previous studies, the average postoperative pain score during coughing for the EA and SA groups is estimated to be  $3.0 \pm 1.7$  and  $4.4 \pm 1.7$ . To achieve a statistical power of 80% with a two-sided significance level of 5%, 24 patients per group are required. Sixty patients (30 per group) are required, accounting for a dropout rate of 20%. This pilot trial is intended to establish initial data for the primary outcome measure, and the results will be used to calculate the sample size for the next larger randomized controlled trial.

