## **Statistical analysis**

Statistical analysis will be processed using SPSS Statistics 27. Measurement data will be described as mean  $\pm$  standard deviations ( $M \pm SD$ ), median, or interquartile range. Categorical data will be presented by frequency, percentage, or constituent ratio. Independent t-test or

Wilcoxon rank-sum test will be used to compare the measurement data between groups. The chi-squared test or Wilcoxon rank-sum test will be used to compare the categorical data between groups. The significant level is  $P < 0.05$ , which is considered to be statistically significant.

All randomly assigned patients will be included in the intention-to-treat (ITT) analysis. The per-protocol (PP) analysis, which includes participants completing 80% of the treatment without major protocol deviations or omissions will be used for the primary outcome as sensitivity analysis.

Normally distributed continuous variables will be analyzed using independent t-test. Skewed continuous variables will be analyzed using Wilcoxon rank-sum test. Categorical data will be analyzed using the chi-squared test or Wilcoxon rank-sum test. We will perform a predefined subgroup analysis on primary endpoints according to the chest tube duration, the number of incisions, etc.

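### The primary comparison is valid but unadjusted, and number of incisions is used only to form subgroups too small to inform; adjusting for it would bring a modest gain in precision.

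*Protocol*

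**What the plan says.** For the analysis, the Protocol (Statistical analysis) states: "Normally distributed continuous variables will be analyzed using independent t-test". Skewed variables go to the Wilcoxon rank-sum test. No covariate is named.

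Number of incisions appears once in the Protocol, in the same section: "We will perform a predefined subgroup analysis on primary endpoints according to the chest tube duration, the number of incisions, etc". One blanket threshold of P < 0.05 applies to all tests.

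Three other places bear on the point:

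- **Randomization:** allocation is stratified by the two centres only, so incisions and type of resection are balanced by chance alone.
- **Inclusion criteria, item 3:** several operations are admitted together, "including lung wedge resection, segmentectomy, and pulmonary lobectomy".
- **Interventions:** the first session is given when the patient returns to the ward, so the surgical factors are already set by then.

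On size, the Sample size calculation section says "To achieve a statistical power of 80% with a two-sided significance level of 5%, 24 patients per group are required" and describes the study as a pilot: "This pilot trial is intended to establish initial data for the primary outcome measure".

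**The concern.** Number of incisions has to be recorded for the planned subgroups, and the EA or SA sessions cannot alter it, because the first one follows surgery. That makes it a natural candidate for adjustment. The plan instead uses it only to divide a 60-patient trial.

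Two things are at stake. First, the subgroup results will be too imprecise to show either a difference or its absence, yet nothing in the plan stops them from being read by P-value. Second, if incisions do predict cough pain, the unadjusted comparison leaves explainable variation in the error term. It also gives an estimate that moves with whatever imbalance this one trial happens to show. Since the results are to feed the sample size of a larger trial, both the estimated difference and its SD matter.

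**Working it through.** **Inputs from the documents.** Means 3.0 (EA) and 4.4 (SA), so a difference of 1.4; common SD 1.7; two-sided 5%; 80% power; 24 per group; 20% dropout (all from Sample size calculation).

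**Inputs assumed, because the documents give none.** The split between one and more than one incision: 50/50, with 80/20 as a check. The gap in mean cough NRS between the incision groups: 0.5 to 1.0 point.

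**1. The plan's own figure.** n = 2 × [1.7 × (1.960 + 0.842) / 1.4]² = 23.15, rounded up to 24 per group; 24 / 0.80 = 30 per group, 60 in total. The plan's figures reproduce. By the noncentral t distribution, power at 24 per group is 79.8%.

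**2. Incision subgroups (even split, 12 per arm in each half).**
- Power for a 1.4-point effect within one half, noncentral t with 22 df: 48.8%. With no dropout (15 per arm) it is 58.6%.
- SE of the difference between the two subgroup effects: 1.7 × √(4/12) = 0.98. The 95% half-width is 1.96 × 0.98 = 1.92, or 1.98 with the t quantile on 44 df. Either way it is wider than the 1.4-point effect the trial is sized for.
- Power for an interaction as large as 1.4: about 30% at 48 patients and 36% at 60.

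**3. What adjustment could gain.** For a two-level factor with share p and gap g, R² = p(1 − p)g² / 1.7², and the residual SD is 1.7 × √(1 − R²). At 24 per arm:

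| Split | Gap (NRS) | R² | SE of difference | Power for 1.4 |
|---|---|---|---|---|
| none (unadjusted) | – | 0 | 0.491 | 79.8% |
| 50/50 | 0.5 | 0.022 | 0.485 | 80.5% |
| 50/50 | 1.0 | 0.087 | 0.469 | 83.1% |
| 80/20 | 0.5 | 0.014 | 0.487 | 80.2% |
| 80/20 | 1.0 | 0.055 | 0.477 | 81.9% |

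The adjusted rows use 44 df (48 patients less intercept, arm, centre and incisions) and credit centre with no explained variance. The even split is the most favourable case.

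**4. Chance imbalance.** With a 50/50 split, a difference between arms of 20 percentage points or more arises in 19.3% of trials with 24 per arm (15.5% with 30 per arm), by exact binomial enumeration. It moves the unadjusted estimate by 0.20 × g, that is 0.10 to 0.20 NRS for gaps of 0.5 to 1.0. The 95% half-width of the unadjusted difference is 0.99.

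**5. Is the unadjusted test invalid?** No. Simulated type I error with a 1.0-point gap was 4.9% overall. Among trials with an imbalance of 20 points or more, it was about 5.5% for a 0.5-point gap and about 7% for a 1.0-point gap, offset by a rate below 5% in the better-balanced trials.

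**The case against.** The strongest case against is that nothing here is an error. The unadjusted test matches the sample size calculation, which reaches its power without covariates. Covariates are often left to the SAP, which is not at hand, and the trial is a pilot. All of that stands, and it keeps the point at the level of an improvement. The Protocol does, however, state both the test and the role of incisions, so that stated choice can be commented on.

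Two stronger readings are tempting, and the documents support neither.

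- **That the plan itself treats incisions as a determinant of pain.** The Background says "Acute postoperative pain is closely related to operation time, chest tube duration, and postoperative activities"; it lists neither incisions nor type of resection. Choosing a subgroup factor presumes possible effect modification, not necessarily prognosis. The gap used above is therefore an assumption.
- **That chance imbalance in surgical extent biases the result.** Under randomisation it is random error already covered by the t-test's standard error, as step 5 shows. What remains true is narrower: given an imbalance actually seen, adjustment reduces its effect on the estimate.

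A further reservation concerns timing. The documents do not say whether randomisation precedes surgery. Some criteria, such as conversion to open surgery as an exclusion, can only be settled at or after the operation, but that does not fix the order. If randomisation comes first, number of incisions is a post-randomisation variable, though still one set before any session, and its use as a covariate needs that justification in writing.

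**Conclusion.** The point holds as a modest suggestion on precision. The subgroup part is the firmer half: with the plan's own SD and evaluable numbers, and an even split assumed, each incision subgroup has about 49% power for the full planned effect, and the contrast between subgroups is known only to within about 2 NRS points. An uneven split would make the contrast less precise still.

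The covariate part is right in direction and small. Under assumed gaps of 0.5 to 1.0 point, adjustment adds roughly 0.5 to 3.5 percentage points of power at 24 per arm. If incisions do not predict cough pain, it adds nothing and costs one degree of freedom. No figure can be given for extent of resection, because the documents offer nothing to base one on.

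**What to change.** Pre-specify, before unblinding, a linear model of the 72 h average cough NRS on arm, centre (the only stratification factor) and number of incisions (one versus more than one). Extent of resection (wedge or segment versus lobe) may be named as an optional further covariate. Report the adjusted mean difference with its 95% CI.

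Keep the t-test, or the Wilcoxon test if the data are skewed, as a supporting analysis, so that the existing provision for skewed data is not lost. Show the incision subgroups as estimates with 95% CIs and without subgroup P-values. State when randomisation takes place relative to surgery, so that incisions can be defended as a covariate.

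The cost is a few sentences in the analysis section, one degree of freedom for each surgical covariate and one for centre, and a little more analysis work. Number of incisions must be recorded anyway for the planned subgroups.

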### **Drop-out case and handling**

Drop-out criteria: although the subjects through informed consent and obtained the random number by qualified screening, they could not complete the course of treatment and observation period stipulated in the study protocol, which was regarded as a drop-out case.

Handling of drop-out cases: When the subjects drop out, the researcher

should contact the subjects as much as possible by visiting the house, making an appointment for follow-up, telephone, and letter, asking for reasons, recording the last acupuncture time, and completing the evaluation items that can be completed. The relevant study data of drop-out cases should be properly preserved, which is not only for keeping, but also for ITT analysis. Patients who drop out do not need to be recruited.

### **Withdraw criteria**

The subject proposed to withdraw:

- ① Poor curative effect;
- ② Can't tolerate adverse events;
- ③ Hope to take other treatment methods;
- ④ Withdraw voluntarily without any reason.

### **Termination standard**

- ① The patient has serious adverse events, and the clinical trial of this case needs to be stopped according to the doctor's judgment.
- ② If other diseases affect the observation of the trial, the clinical trial should be stopped according to the doctor's judgment, and the case should be treated as invalid.
- ③ There are important deviations in the implementation of the clinical study protocol, such as poor compliance, which makes it difficult to

evaluate the efficacy of acupuncture.

- ④ The subject is unwilling to continue the clinical trial during the clinical trial and asks the competent doctor to withdraw from the clinical trial.

### **Elimination criteria**

- ① Subjects entered the trial in violation of inclusion criteria and exclusion criteria.
- ② Combined medication in violation of the study protocol.
- ③ Wrong treatment grouping.
- ④ The subjects' medication compliance is very poor.

### **Quality control**

- ① Subjects will be included in strict accordance with the criteria of diagnosis, inclusion, and exclusion.
- ② The random number is managed by the independent administrator. The random number is given only after obtaining the specific information of qualified subjects and recording it, so as to ensure the allocation concealment and prevent the random number from leaking or drifting in advance.
- ③ After discussion by experts, the relevant standard operating procedures are formulated for each step of the experiment, so that there is a unified standard for the operation of each step and a basis to follow when

opinions differ.

- ④ Researchers must undergo unified training. The contents include being familiar with the objectives and requirements of this study, mastering the relevant diagnosis and treatment standards, random distribution methods, acupuncture operation methods, and the use of evaluation forms, and setting different training periods for researchers with different divisions. Researchers with the same division of labor in the research center need to pass the consistency test to carry out the experiment, and the consistency test is required to use video materials for film preservation.
- ⑤ The research sub-center inspectors monitor completed cases twice a month, identify the existing problems, and guide them to correct.
- ⑥ The inspectors of the research center review the study process and examine the ethical issues involved in the study. Order them to rectify if they do not comply with the ethical principles. Regularly and irregularly monitor the study process, point out the existing problems and guide them to correct.

## **Risk and Management**

### **Acupuncture Risk**

Evaluation of adverse events at any time in the process of acupuncture includes hematoma, fainting, continuous post-needling pain, etc.

### **Treatment measures for fainting needle**

Stop acupuncture, pull all the needles out, and ask the patient to prostrate and keep warm.

### **Treatment measures for hematoma**

When a small piece of bruise is caused by a small amount of subcutaneous bleeding, it generally does not need to be treated, and it can subside on its own. When the local swelling and pain are severe and the bruised area is large, a cold compress should be used to stop bleeding.

### **Treatment measures for continuous post-needling pain**

If the severity of continuous post-needling pain is mild, it can disappear or improve by local upward and downward patrol with fingers. In addition to local upward and downward patrol, moxibustion with moxa sticks can also be used for severe continuous post-needling pain, which can also be quickly eliminated.

## **Summary and Data Preservation**

After the clinical observation is completed, the project management office is responsible for summarizing the data. All the original materials are reviewed and signed by the person in charge of the sub-center. The scientific research department will seal it and keep it in the scientific research data archives of the project undertaking unit.
